#### Intervention

Participants will begin the 8-week intervention for the PR maintenance program in either the onsite or remote group depending on their group allocation, with supervised visits occurring once a week for both groups and regular reminders for the meetings sent to participants. At the initial treatment session, each participant will receive printed educational materials from the COPD Foundation [44] and the Pulmonary Fibrosis Foundation [45]. These resources will cover topics such as living well with CLD, the impact of smoking, and creating a CLD action plan, including disaster preparedness. Both groups will participate in a weekly 60-minute supervised session. Supervised sessions will be delivered in-person for the onsite group and remotely via video conferencing for the tele-rehab group. The intervention intensity will be determined by the distance covered in 6MWT conducted at baseline. Licensed physical therapists from the study team who have expertise in managing chronic conditions will deliver all the interventions. These therapists will receive specific training on the study protocol to ensure consistency in intervention delivery. All interventions will adhere to the research protocol outlined in Table 1.

#### Onsite Group

The supervised 60-minute session for onsite participants will include multiple components. The session will begin with a brief check-in to review the participant's weekly activities at home and any changes in symptoms, followed by education on self-management strategies for airway clearance and the importance of maintaining regular physical activity. Breathing retraining will involve inspiratory muscle training using the Threshold Inspiratory Muscle Trainer Respironics PEP at 30% to 50% of maximal inspiratory pressure. After the breathing exercises, participants will complete a 25-minute aerobic exercise training session, preceded by a short warm-up. Aerobic training will be performed using available equipment such as a NuStep, treadmill, cycle ergometer, or through overground activities, including walking or stair climbing. The training intensity will be prescribed based on the baseline 6MWT results. Peak oxygen consumption (VO_2_) will be estimated using published regression equations [46]. Training will be conducted at 60%-85% of VO_2_ reserve and converted to walking distance and speed using the American College of Sports Medicine walking equations for treadmill and overground walking [47]. For nonwalking activities such as cycling or stair climbing, a corresponding rate of perceived exertion of 13-16 will be used. Aerobic training may be completed as a continuous 25-minute session or divided into intervals (eg, 2 × 12.5 minutes or 3 × 8.3 minutes) if symptoms limit continuous exercise.

Following aerobic training, functional strength exercises focusing on lower extremity muscles, including partial squats, sit-to-stand exercises, lunges, and step-ups/step-downs, will be performed. Each session will conclude with a short cool-down period. The details of the intervention sessions are outlined in Table 1. Participants will also be asked to maintain a daily physical activity log and report any planned or unplanned physician visits, emergency room visits, falls, or injuries. The attendance for each session will be recorded.

#### Tele-Rehab Group

Participants in the tele-rehab group will follow the same intervention protocol as the onsite group described above, with the mode of aerobic exercise adjusted based on available equipment (see Table 1). Each tele-rehab participant will receive a respiratory muscle training inspiratory muscle trainer device for home use. The intervention will be delivered remotely via established tele-rehabilitation models using a tablet computer. iPads will be loaned to participants as needed for the duration of the study. Videoconferencing will be conducted via research-grade Zoom teleconferencing [48], which will enable participants to see and speak to the supervising physical therapist. To ensure the safety of participants and proper understanding of equipment use and the exercise program, we will conduct the initial training session and home exercise program setup during the initial onsite visit. The fidelity of the exercise intervention for both groups will be maintained through regular staff training, audits of exercise prescription and progression, and monitoring of participant engagement.

### Statistical Analysis

Since a large 2-group comparative study has not yet been published, this pilot study will generate an estimate of variance and the percentage of change in outcomes needed to determine the power and sample size for a larger study. Therefore, estimation rather than statistical testing is the main objective of this study. Given the possibility of attrition from dropouts, we will recruit 40 participants with a goal to have 30 participants complete the study (15 in each group). Descriptive statistics will be used to summarize the demographic and clinical characteristics and outcomes for all the participants. Feasibility will be assessed using frequency distributions of session adherence and use of activity logs. Comparisons between groups on all outcomes at preintervention and postintervention will be conducted with the intention to treat using a mixed analysis of variance. Within-group comparisons at all 3 time points will be conducted via a repeated measures analysis of variance. Adherence to the program between groups will be compared using independent 2-sided *t* tests. Finally, descriptive statistics with frequency distributions of adverse events, planned and unplanned physician visits, and frequency of use of daily activity log will be reported.

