**Results:**

Recruitment for this institutional review board—approved study (approval date: July 25, 2023) began in January 2024, with 11 (37%) of the 30 participants enrolled to date. This study will generate data comparing tele-rehab and onsite rehabilitation in terms of the primary and secondary outcomes. Use data such as program adherence and attrition will also be reported. The results will inform the feasibility, adherence, and effectiveness of tele-rehab as a sustainable alternative to onsite maintenance rehabilitation. The study is anticipated to be completed by April 2026.

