**Conclusions:**

This study hypothesizes that both tele-rehab and onsite programs will significantly improve clinical outcomes, with tele-rehab yielding comparable benefits to onsite maintenance. Findings will provide evidence supporting accessible and sustainable maintenance rehabilitation options for patients with CLD and guide future large-scale efficacy trials.

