#### Outcome Assessments

Outcomes will be recorded in-person at 3 time points: at baseline before the intervention (time0), at the end of the 8-week intervention (time1), and at 1-month post intervention during follow-up (time2). A blinded study team member will conduct all outcome assessments at each time point (Table 1), with reminder emails sent to participants during the week the assessment is scheduled. Feasibility outcomes will include the number of sessions attended post randomization, the ease of using equipment and procedures, optimal session length, and adherence as measured by the daily activity log. Clinical outcomes will include baseline vitals such as heart rate, respiratory rate, oxygen saturation measured with a pulse oximeter, Borg rating of perceived exertion [33], and modified Medical Research Council dyspnea scale [34,35]. Respiratory muscle strength will be evaluated using maximal inspiratory pressure, while physical function will be assessed with the 30-second chair rise test [36] and the 10-meter walk test [37]. Functional capacity will be measured through 6MWT [38,39] and the 10-meter incremental shuttle walk test [40]. Physical activity will be assessed using the International Physical Activity Questionnaire [41], and the quality of life will be evaluated with the Patient-Reported Outcomes Measurement Information System Global Health Questionnaire [42] and the COPD Assessment Test [43]. Secondary outcomes will include planned or unplanned physician visits, emergency room visits, falls, and injuries.

**Table 1 table1:** Interventions provided for tele-rehab^a^ and onsite rehab^b^ groups.

Goal (duration)	Tele-rehab group and onsite rehab group
Check-in and education (5 min)	Review of activities during the week at home Symptom changes during the week Education on self-management of airway clearance Education on the importance of maintaining regular physical activity
Breathing retraining (5 min)	Inspiratory muscle training using a Threshold Inspiratory Muscle Trainer at 30%-50% of maximal inspiratory pressure
Warm-up (5 min)	Spot marching Stretching large group muscles

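### The plan says it is for estimation, yet it tests every unranked clinical outcome, names no primary outcome and hypothesizes significant improvement; scattered significant results should not be read as support

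*Protocol article*

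**What the plan says.** Four parts of the protocol article bear on this.

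- **Purpose of the analysis.** Statistical Analysis says the pilot is to supply variance and change estimates for sizing a larger study, and puts estimation ahead of testing. Limitations expects too little power to judge efficacy.
- **Planned tests.** The same Statistical Analysis section states: "Comparisons between groups on all outcomes at preintervention and postintervention will be conducted with the intention to treat using a mixed analysis of variance". It continues: "Within-group comparisons at all 3 time points will be conducted via a repeated measures analysis of variance". The only sidedness given is for adherence: "Adherence to the program between groups will be compared using independent 2-sided *t* tests". No alpha is stated.
- **Outcome ranking.** The abstract's Results paragraph promises data "comparing tele-rehab and onsite rehabilitation in terms of the primary and secondary outcomes". Outcome Assessments uses one of those two labels: "Secondary outcomes will include planned or unplanned physician visits, emergency room visits, falls, and injuries". Nothing is called primary. The clinical measures are listed side by side, starting with "Clinical outcomes will include baseline vitals such as heart rate, respiratory rate, oxygen saturation measured with a pulse oximeter, Borg rating of perceived exertion" and going on to strength, function, walking capacity, activity and quality of life.
- **Hypothesis.** The abstract's Conclusions paragraph expects that "both tele-rehab and onsite programs will significantly improve clinical outcomes", with the two modes comparable. The Introduction's hypothesis also speaks of comparable improvement but makes no mention of significance.

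**The concern.** The stated purpose and the planned analysis do not match. A study meant to estimate would report between-arm differences and their precision. This one plans an ANOVA on every outcome between arms and again within groups, and frames its expected result as significance. Because the abstract's primary label is attached to nothing, a reader of the results cannot tell which comparison was meant to carry weight.

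Two things are at stake. First, with many unranked tests, some will probably reach significance by chance, and the abstract's wording invites those to be presented as support. Second, the pilot is meant to inform a larger trial. An outcome carried forward because it looked best among 13 tends to show an inflated effect, which would make the next trial too small. Functional capacity has two tests (6-minute walk and incremental shuttle walk) and quality of life has two instruments (PROMIS Global Health and COPD Assessment Test), with no statement of which leads if they disagree.

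**Working it through.** The plan gives no alpha, power or error rate, so there is no figure of its own to reproduce.

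**Inputs from the documents**
- Clinical outcomes (Outcome Assessments): heart rate, respiratory rate, oxygen saturation, Borg exertion and mMRC dyspnea (5); maximal inspiratory pressure, 30-second chair rise and 10-meter walk (3); 6-minute walk and incremental shuttle walk (2); IPAQ, PROMIS Global Health and COPD Assessment Test (3). Total 5 + 3 + 2 + 3 = 13, or 10 without the three vital signs.
- Between-arm tests: 13. Within-arm tests: 13 × 2 arms = 26.
- Completers: 15 per arm (Statistical Analysis).

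**Assumptions**
- Two-sided 0.05 per test, no adjustment, no true change and no true difference.
- Pairwise correlation between outcomes from 0 to 0.8, central value 0.5; correlation between visits within a person 0.7.
- The between-arm test is the group-by-time term on pre/post data, which is equivalent to a t test on change. The within-arm test is a one-way repeated measures ANOVA over three visits.

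**Step 1: independent outcomes.** The chance of at least one false positive in k tests is 1 − 0.95^k.
- k = 13: 1 − 0.95^13 = 0.487
- k = 10: 1 − 0.95^10 = 0.401
- k = 26: 1 − 0.95^26 = 0.736

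**Step 2: correlated outcomes, by simulation (13 outcomes, 15 per arm)**

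| Correlation between outcomes | Any between-arm test | Any within-arm test, either arm |
|---|---|---|
| 0 | 0.50 | 0.74 |
| 0.3 | 0.43 | 0.66 |
| 0.5 | 0.34 | 0.58 |
| 0.8 | 0.20 | 0.37 |

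With 10 outcomes at correlation 0.5 the two rates are 0.29 and 0.52. A separate simulation with visit correlation 0.6 gives 0.34 and 0.58 at correlation 0.5, so the result does not hinge on that input.

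**Step 3: the event the hypothesis describes.** The abstract expects improvement in both programs, so significance in one arm alone does not meet it. The arms are independent, so if P is the either-arm rate, the per-arm rate is 1 − √(1 − P) and the both-arms rate is its square.
- P = 0.58: 1 − √0.42 = 0.352; squared, 0.12
- P = 0.37: 1 − √0.63 = 0.206; squared, 0.04
- P = 0.74: 1 − √0.26 = 0.490; squared, 0.24

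For the same outcome in both arms, with independent outcomes, the chance is 1 − (1 − 0.05²)^13 = 0.03. The three-visit F test also has no direction, so chance improvement in particular is rarer than these figures.

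**Step 4: sensitivity to alpha.** At 0.01 per test with independent outcomes, the rates in Step 1 fall to 0.12 for 13 tests and 0.23 for 26.

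**The case against.** The strongest reply is that this is a feasibility pilot that already limits its inference. It puts estimation first, concedes low power, places feasibility first among its aims, and uses the word *significantly* in its hypothesis only in the abstract. Such a pilot needs no family-wise error control and need not rank its clinical measures as a confirmatory trial would. All of this stands, and it is why no correction is asked for.

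A stronger reading is tempting: that 13 outcomes are tested at full alpha, so that a false claim of significant improvement is likely. The documents do not support it, for three reasons.

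- No alpha is given. The level, any multiplicity rule and the deciding ANOVA term may sit in a full protocol or analysis plan that is not shown, so their absence from the article is not a fault.
- The between-arm rate of 0.34 is below one half and bears on a difference between arms. The trial expects the arms to be comparable, so a chance difference would count against its hypothesis.
- The within-arm rate of 0.58 counts significance in either arm, whereas the hypothesis names both. For both arms the rate is about 0.12.

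The count of 13 also includes three items introduced as baseline vitals. Without them it is 10, and the rates drop only modestly.

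What the reply does not remove is the contradiction within the article. It declares estimation, plans tests on everything, refers to a primary outcome it never names, and words its hypothesis as significance.

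**Conclusion.** The point holds as an inconsistency between stated purpose and planned analysis. It does not hold as a demonstrated inflation of the error rate for the trial's own hypothesis.

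The error rates are illustrations resting on an assumed 0.05 per test, 15 completers per arm and equal correlation among outcomes. They show that isolated significant results are to be expected even if nothing changed, while significance in both arms by chance is uncommon. Scattered p-values are thus a poor basis either for declaring the hypothesis met or for selecting the endpoint of the larger trial. The matter should be corrected, but it does not threaten the conduct of the study.

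**What to change.** Before the analysis planned for April 2026:

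1. In Outcome Assessments, name the primary feasibility outcome and one lead clinical outcome, so that the abstract's reference to primary outcomes has a referent.
2. In Statistical Analysis, make the lead contrast the between-arm difference at the end of the 8-week intervention (time1), adjusted for the baseline (time0) value, reported as an estimate with a 95% CI.
3. Choose the lead outcome without reference to the remark in the article's Results section comparing 6-minute walk scores of one participant in each arm. If the 6-minute walk is chosen, disclose that remark.
4. Label all other clinical outcomes and all within-arm analyses exploratory, reported as estimates with confidence intervals.
5. Reword the hypothesis in the abstract's Conclusions to drop the significance claim, in line with the Introduction and with the estimation aim.

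No multiplicity correction is needed. The cost is a few sentences and a registry update, with no extra participants, visits or data. The small downside is that outcomes other than the named one cannot be claimed as significant improvements.

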**Methods:**

This randomized, assessor-blinded feasibility pilot trial will enroll 30 participants who have completed outpatient PR. Participants will be randomized into 2 groups: (1) tele-rehab, involving remotely supervised sessions conducted via videoconferencing or (2) onsite maintenance rehabilitation with in-person sessions. Both groups will receive weekly supervised sessions for 8 weeks facilitated by licensed physical therapists. Assessments will be conducted onsite at baseline, after the 8-week intervention, and at 1-month follow-up by a blinded assessor. The feasibility of the intervention and the study methods will be assessed by the log-in into the number of sessions attended after randomization, the ease of using the equipment and procedures, optimal session length, and adherence to the intervention protocol. Clinical outcomes will include dyspnea and perceived exertion, respiratory muscle strength, physical function, 6-minute walk distance, physical activity, and quality of life. Descriptive statistics with means and standard deviations for continuous and frequency distributions for categorical data will be utilized to report individual and group characteristics. Feasibility outcomes will be compared using independent 2-sided *t* tests. Between-group comparisons will use mixed analysis of variance, and within-group comparisons will be analyzed with a repeated measures analysis of variance.

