### Study Design

This study follows the CONSORT (Consolidated Standards of Reporting Trials; Multimedia Appendix 1) and SPIRIT (Standard Protocol Items: Recommendations for Interventional Trials; Multimedia Appendix 2) guidelines. The study will be a randomized, assessor-blinded, pilot feasibility trial. Participants will be randomly assigned in a 1:1 allocation ratio to either (1) a tele-rehab group with remotely supervised intervention or (2) an onsite group with in-person supervision. Figure 1 outlines the study design and recruitment process. The anticipated study period is from September 1, 2023, to April 1, 2026.

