#### Random Assignment

Following the baseline assessment, a separate research team member will contact each participant via phone to communicate the randomized group assignment. Participants will be randomly assigned to one of the 2 groups: (1) tele-rehab, where the participants receive supervised intervention remotely at home or (2) onsite outpatient rehabilitation. A web-based randomization service [32] will be used to generate random assignments to eliminate allocation bias.

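### The between-arm analysis treats the baseline value as a second outcome in a pre/post mixed ANOVA; adjusting for it as a covariate would give a more precise arm difference from the same data unless the pre-post correlation is very high

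*Protocol article*

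**What the plan says.** The protocol article fixes the between-arm method in two places. The Statistical Analysis section reads: "Comparisons between groups on all outcomes at preintervention and postintervention will be conducted with the intention to treat using a mixed analysis of variance". The abstract's Methods paragraph agrees: "Between-group comparisons will use mixed analysis of variance, and within-group comparisons will be analyzed with a repeated measures analysis of variance". Neither place names a baseline covariate, and neither says which term of the mixed ANOVA is the arm effect. Within-arm change is handled separately: "Within-group comparisons at all 3 time points will be conducted via a repeated measures analysis of variance".

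The design makes a clean baseline available. Outcome Assessments places the first measurement (time0) before the intervention, with later ones at the end of the 8 weeks (time1) and one month afterwards (time2). Random Assignment adds: "Following the baseline assessment, a separate research team member will contact each participant via phone to communicate the randomized group assignment". On size and allocation, Study Design says "Participants will be randomly assigned in a 1:1 allocation ratio", and Statistical Analysis plans to recruit 40 so that 30 complete, 15 per arm. On purpose, Statistical Analysis says: "Therefore, estimation rather than statistical testing is the main objective of this study". It adds that the pilot should supply a variance estimate for sizing a larger study.

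**The concern.** Each clinical outcome has a value taken before participants learn their arm, by an assessor blinded to allocation. That value cannot carry an arm effect and is usually among the best available predictors of the time1 value. A pre/post mixed ANOVA uses it only as the first of two outcome levels. The group-by-time contrast then subtracts the whole baseline value, whereas ANCOVA subtracts only the part that predicts the time1 value.

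At stake is the width of the interval for tele-rehab versus onsite, which is the natural product of an estimation study. With about 15 per arm, chance baseline differences between arms can be sizeable, and an unadjusted change comparison passes part of any such difference into the estimate. The protocol gives no reason for leaving the baseline out as a covariate.

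**Working it through.** **No figure to reproduce.** The protocol states no alpha, power, effect size, SD or pre-post correlation for this comparison. The only design numbers are the 1:1 allocation and n = 15 completers per arm.

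**Assumptions.** Outcome SD = 1 at both time0 and time1, and pre-post correlation rho, varied from 0.3 to 0.95 because the document gives none.

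**Step 1: what the group-by-time term is.** In a two-arm, two-time mixed ANOVA, the interaction F equals the squared t from a two-sample test on change scores. On one simulated data set, both came to 2.6165.

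**Step 2: variances of the arm difference.**
- Change scores: (2/n) × 2(1 − rho).
- ANCOVA: (2/n) × (1 − rho²) × [1 + 1/(2n − 4)]. The bracket is the average cost of estimating the slope. At n = 15 it is 1 + 1/26 = 1.038.
- Ratio of ANCOVA to change scores: (1 + rho)/2 × 1.038.

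| rho | (1 + rho)/2 | ratio at 15 per arm |
|---|---|---|
| 0.3 | 0.65 | 0.68 |
| 0.5 | 0.75 | 0.78 |
| 0.7 | 0.85 | 0.88 |
| 0.8 | 0.90 | 0.93 |
| 0.9 | 0.95 | 0.99 |
| 0.95 | 0.975 | 1.01 |

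Break-even: (1 + rho)/2 × 27/26 = 1, so rho = 52/27 − 1 = 0.926, or about 0.93.

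**Step 3: interval width at rho = 0.5.**
- Change scores: SE = √(2/15 × 1.00) = 0.365. With t(28) = 2.048, the half-width is 0.75 SD.
- ANCOVA: SE = √(2/15 × 0.75 × 1.038) = 0.322. With t(27) = 2.052, the half-width is 0.66 SD.

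**Step 4: check by simulation** (20,000 trials per rho, 15 per arm, illustrative true difference 0.80 SD). The variance ratios were 0.78, 0.88, 0.93 and 0.98 at rho 0.5, 0.7, 0.8 and 0.9. The mean half-widths, change scores versus ANCOVA, were 0.74 vs 0.65, 0.57 vs 0.54, 0.47 vs 0.45 and 0.33 vs 0.33 SD. These run slightly below Step 3 because a sample SD averages a little under the true SD. At rho 0.5 the mean estimates were 0.80 for the interaction contrast, 0.80 for ANCOVA and 0.40 for the group main effect.

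**Step 5: where the lost precision comes from.** Given an observed baseline difference d between arms, the change-score estimate is shifted on average by −(1 − rho)d. The standard error of d at 15 per arm is √(2/15) = 0.365 SD. A one-standard-error imbalance at rho 0.5 therefore moves the estimate by 0.5 × 0.365 = 0.18 SD. Over repeated trials this averages to zero. Its variance, (2/n)(1 − rho)², added to the large-sample ANCOVA variance (2/n)(1 − rho²), gives (2/n) × 2(1 − rho), the change-score variance. Imbalance sensitivity and lost precision are thus one effect, not two.

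**The case against.** The strongest reply is that the planned method is valid. The group-by-time contrast is unbiased under randomisation, it does use the baseline through the change, and its intervals already allow for chance imbalance. That stands: the point concerns efficiency, not bias.

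The reply continues that the gain depends on a correlation the protocol does not give, and is small for highly repeatable measures. That also stands. At rho 0.8 the half-widths are 0.47 and 0.45 SD, and at 0.9 they do not differ to two decimals. A reader might infer that ANCOVA wins for every rho below 1. That is a large-sample statement and fails above about 0.93 at this size.

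Two further inferences are tempting, and the document supports neither.
- **The arm effect will be halved.** The group main effect averages pre and post and would estimate half the post-treatment difference. No section says that this term will be reported as the arm effect. The stated interest in percentage change points rather to group-by-time, and naming the term may be left to a fuller plan.
- **The larger trial will inherit a change-score variance.** The protocol promises only a variance estimate. With equal SDs (s at both times), the mixed ANOVA yields a between-subject mean square estimating s²(1 + rho) and a within-subject one estimating s²(1 − rho). Their product divided by their average is s²(1 − rho²), so the adjusted variance can be recovered.

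Loss of power is also a weak argument here, since Limitations already expects the trial to be underpowered for efficacy.

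The reply does not remove the core. The article commits to this model in two places, estimation is its declared aim, and a more precise estimator is available from data already being collected.

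**Conclusion.** The point holds as a modest improvement in precision that is almost free. The planned comparison is unbiased but generally less precise than baseline adjustment. At 15 per arm the variance saved is about 32% at rho 0.3, 22% at 0.5, 12% at 0.7, 7% at 0.8 and 1% at 0.9, with nothing gained above about 0.93. At rho 0.5 the 95% CI half-width drops from about 0.75 to 0.66 SD.

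These figures rest on equal SDs at the two times, a linear pre-post relation, 15 analysed per arm and an assumed rho. They should not be read as showing bias, a halved effect or a commitment to a particular variance for the next trial.

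**What to change.** In Statistical Analysis, replace the between-group sentence for continuous clinical outcomes. Estimate the arm difference at time1 by ANCOVA, with the time1 value regressed on arm and that outcome's time0 value, or by an equivalent mixed model with time0 as covariate. Name the adjusted arm coefficient as the between-arm estimate and report it with its 95% CI. Also report the residual SD and the pre-post correlation for each outcome, so that the larger trial can be sized under either analysis. Change the matching sentence in the abstract.

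The cost is one degree of freedom per outcome, no gain where rho exceeds about 0.93, and the report to the institutional review board that Ethical Considerations requires for protocol changes. No new data, visits or participants are needed. The change should be dated before the analysis that the Results section expects to start by April 30, 2026.

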One method to improve adherence in maintenance programs is telerehabilitation (tele-rehab), which is a way of participating in medical appointments via a technology device [17]. Tele-rehab is a viable alternative rehabilitation approach for patients with CLD and holds potential as an effective tool for increasing positive behavioral changes, including long-term adherence and a more physically active lifestyle [18-21]. Few studies [18,22-24] have compared the benefits of tele-rehab versus onsite PR on health outcomes in people living with CLD, and even fewer studies have compared supervised maintenance programs delivered via tele-rehab with onsite maintenance, leaving many gaps in the literature [25]. Furthermore, most studies are limited to people with COPD, with only a small number investigating the effects of tele-rehab on other CLDs [26,27].

Given these limitations, there is a clear need for well-designed feasibility studies to evaluate the effectiveness and practicality of supervised maintenance programs, particularly those delivered via telehealth. The purpose of this pilot feasibility trial is to (1) assess the feasibility of delivering an 8-week supervised maintenance program remotely via tele-rehab in comparison to onsite delivery and (2) compare the effectiveness of these interventions on clinical outcomes in patients with CLD. We hypothesize that tele-rehab will be feasible to implement, with acceptable adherence, and will yield comparable improvements in clinical outcomes to onsite rehabilitation.

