### Conclusions

This pilot randomized feasibility trial aims to address critical gaps in the long-term management of CLD by comparing onsite and tele-rehab supervised maintenance programs. The study emphasizes the importance of overcoming traditional barriers to PR, such as transportation challenges and limited facility availability while promoting equitable access to care. By focusing on improving self-efficacy and adherence to health-enhancing behaviors, this intervention has the potential to sustain the benefits of PR beyond discharge and reduce adverse health outcomes. The trial will provide valuable data on feasibility, adherence, and clinical outcomes for tele-rehab and onsite programs, providing insights for the development of larger-scale trials. Additionally, this study addresses the growing need for innovative care models that incorporate technology to enhance patient outcomes and reduce health care disparities. Despite the acknowledged limitations such as the small sample size, language restrictions, and the potential for dropout, the findings will contribute valuable information to guide future efficacy trials. This trial has the potential to inform future standards of care for patients with CLD by demonstrating the feasibility of accessible and effective tele-rehabilitation maintenance programs to sustain long-term health benefits.

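### On its natural reading, the plan gives the 1-month follow-up, the only visit after supervision ends, no between-arm estimate

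*Protocol article*

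**What the plan says.** The Outcome Assessments section schedules in-person assessment of both arms "at baseline before the intervention (time0), at the end of the 8-week intervention (time1), and at 1-month post intervention during follow-up (time2").

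The Statistical Analysis section assigns these visits to analyses in two adjacent sentences:

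- Between arms: "Comparisons between groups on all outcomes at preintervention and postintervention will be conducted with the intention to treat using a mixed analysis of variance".
- Within arms: "Within-group comparisons at all 3 time points will be conducted via a repeated measures analysis of variance".

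The Methods part of the Abstract names the same two techniques without time points: "Between-group comparisons will use mixed analysis of variance, and within-group comparisons will be analyzed with a repeated measures analysis of variance". The second purpose stated in the Introduction is to "compare the effectiveness of these interventions on clinical outcomes in patients with CLD". The Statistical Analysis section also says that estimation, not testing, is the main objective, and that the pilot is to supply the variance and change figures for a larger study.

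**The concern.** The between-arm sentence names two occasions and the within-arm sentence names three. On that wording, time2 enters only the within-arm analysis.

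Time2 is the only visit after the weekly supervised sessions have stopped. It is therefore the only visit that can show whether carry-over after the maintenance programme differs between remote and onsite delivery. The trial randomises, collects these data in both arms and has a comparative aim, yet the article commits to no tele-minus-onsite estimate there.

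Two things are at stake. The larger trial would be designed without a planned estimate of the arm difference at follow-up. And a reader who wants that difference would have only two within-arm results to set side by side, which is not a comparison of arms.

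**Working it through.** **1. Which visit enters which analysis**

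| Visit | Collected in both arms | Between-arm mixed ANOVA | Within-arm repeated measures ANOVA |
|---|---|---|---|
| time0, baseline | yes | yes (preintervention) | yes |
| time1, end of 8 weeks | yes | yes (postintervention) | yes |
| time2, 1 month later | yes | not named | yes |

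The Abstract neither adds time2 to the between-arm analysis nor excludes it. No other section of the article plans a between-arm estimate of clinical outcomes at time2.

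**2. The plan's own sample-size figure**

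The Statistical Analysis section recruits 40 to obtain 30 completers, 15 per arm. No dropout rate is stated. The figures imply 1 − 30/40 = 25%, and 30/(1 − 0.25) = 40, so they agree with each other. The article gives no power calculation, effect size, SD or significance level for the clinical outcomes.

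**3. Precision of the missing contrast**

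Assume complete data, equal SDs in the two arms and an ordinary two-sample interval. With n per arm, the 95% CI half-width in SDs of the analysed quantity (for example, change from time0 to time2) is t(0.975, 2n − 2) × √(2/n).

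- n = 15: 2.048 × √(2/15) = 2.048 × 0.365 = 0.75 SD.
- n = 20 (no dropout from 40): 2.024 × √(2/20) = 2.024 × 0.316 = 0.64 SD.

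**4. Why within-arm results cannot replace it (hypothetical illustration)**

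The inputs here are assumptions, apart from n = 15 per arm: the same true change in both arms, a two-sided 5% level, and a paired t test as a simple stand-in for the planned ANOVA. If each within-arm test has power p and the arms are independent, the chance that exactly one is significant is 2p(1 − p).

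| True change in each arm (SD of change) | Power p, n = 15 | 2p(1 − p) |
|---|---|---|
| 0.3 | 0.19 | 0.31 |
| 0.5 | 0.44 | 0.49 |
| 0.7 | 0.71 | 0.41 |

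Across this range, two arms with identical true changes would appear to disagree in 31% to 49% of trials.

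**The case against.** **The word postintervention may cover time2.** The Outcome Assessments section describes the last visit as "at 1-month post intervention during follow-up (time2"), and the Abstract puts no limit on visits. This stands as a real ambiguity, so it would be too strong to say that the article rules out a comparison at time2. The two-visit reading is still the natural one, because the very next sentence uses different words when it means three visits. If three were meant, the same one-sentence clarification is needed.

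**Time2 is not the only evidence on sustained benefit.** A reader might infer that the plan leaves sustained benefit uncompared altogether. The documents do not support that. Participants enter after completing pulmonary rehabilitation, and the Conclusions section says "this intervention has the potential to sustain the benefits of PR beyond discharge", which refers to discharge from that earlier programme. The change from time0 to time1 under weekly maintenance bears directly on this, and it is compared between arms. What lacks a comparison is narrower: carry-over after the maintenance programme itself ends.

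**No section says that one arm's p-value will be set against the other's.** Correct. The discordance figures show why that shortcut would fail; they do not measure an error the authors have planned. Nor does the article say that the repeated measures ANOVA is fitted separately in each arm; that is an inference from its within-group label.

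**This is an estimation pilot, time2 is summarised descriptively, and ±0.75 SD is imprecise.** All true, and the Limitations section expects low power for efficacy. But a summary for each arm does not commit to a between-arm difference or its interval, and an estimation objective is a reason to report that interval, however wide.

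**Conclusion.** The point holds in a limited form. As most naturally read, the Statistical Analysis section confines the between-arm mixed ANOVA to baseline and end of intervention, and uses time2 only within groups. The one assessment after supervised maintenance ends then has no planned between-arm estimate, although it is collected in both arms and the trial has a comparative aim.

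The conclusion rests on the contrast between two adjacent sentences, and a looser reading of one word would weaken it. It does not extend to the time1 comparison, which is planned. At 15 completers per arm the missing estimate would have a half-width of about 0.75 SD, under equal SDs and complete data. It would inform the design of a larger trial and could not establish efficacy or equivalence. The 31% to 49% discordance is illustrative only. This should be corrected; it does not threaten the trial's validity.

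**What to change.** State in the Statistical Analysis section that the between-arm mixed model includes time0, time1 and time2 with a group-by-time term. Report the tele-minus-onsite difference with its 95% CI at time1 and at time2, and make no efficacy claim from either. Within-group changes may stay as description, with a note that they will not be used to infer a difference between arms. Align the Abstract's sentence on the analysis.

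The cost is one or two sentences. Sample size, visits and data collection do not change. The Results section has analysis starting by April 30, 2026, so the wording should be settled before then.
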